#### Sample size calculation

2.2.4

The sample size calculation was conducted using G*Power 3.1.9.7, selecting the F-test family and the “ANOVA: Repeated measures, within-between interaction” option. The calculation targeted the omnibus longitudinal group-by-time interaction in a design with three groups and three assessment points. The effect size was entered as Cohen’s *f* = 0.16, which represents a small effect and is approximately comparable to a standardized effect of *d/g* ≈ 0.32 under a simple two-group contrast approximation, based on prior meta-analytic findings that report small but consistent effects of app-based interventions on psychological well-being among university students (26). To account for the two co-primary outcomes, the alpha level was adjusted to α = .025 using a Bonferroni correction. The remaining parameters were statistical power = .95, correlation among repeated measures = .50, and nonsphericity correction *ϵ* = 1. Under these assumptions, the required analytical sample size was 141 participants, corresponding to 47 participants per group, with an actual power of .9509. To allow for an anticipated attrition rate of approximately 20%, the recruitment target was increased to 177 participants, corresponding to 59 participants per group.

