#### Outcome measures

2.2.7

Participants will be assessed at three key time points: pre-intervention (T1), post-intervention (T2), and six-month follow-up (T3), using the instruments listed in **Table 2**. The evaluated variables will include sociodemographic, academic, and clinical characteristics; presence of mental disorders; emotional well-being; psychological, emotional and social well-being; positive emotion; engagement; relationships; meaning; accomplishment; treatment adherence and dropouts; and satisfaction with the intervention, following the same order presented in **Table 2** and **Figure 1**. All evaluations will be conducted in person by independent psychologists blinded to the study’s objectives, hypotheses, intervention conditions, and group assignments. Evaluator training will be provided by two senior psychologists with extensive experience in psychological assessment and intervention studies, consisting of 20 hours of theoretical and practical seminars, including role-playing scenarios and supervised mock assessments to ensure standardized administration of the instrument. A random sample of 10% of the screening interviews will be audio-recorded and independently rated by a second independent blinded psychologist. Interrater agreement for the final eligibility decision (eligible vs. excluded) will be calculated using Cohen’s kappa, with κ ≥.80 considered the minimum acceptable threshold. Any discrepancies will be resolved by consensus with the senior supervisors.

**Table 2 T2:** Variables, measurement instruments, and administration format.

Variable	Measurement instrument	Administration format
Sociodemographic, academic and clinical characteristics	Sociodemographic, academic, and clinical questionnaire	Hetero-administered
Mental disorders	Structured Clinical Interview for DSM-5, Clinician Version (SCID-5-CV; First et al., 2015)	Hetero-administered
Primary outcomes		
Emotional well-being	Warwick–Edinburgh Mental Well-Being Scale (WEMWBS; Tennant et al., 2007)	Self-administered
Psychological, emotional, and social well-being	Mental Health Continuum–Short Form (MHC-SF; Keyes, 2002)	Self-administered
Secondary outcomes		
Positive emotion	Positive and Negative Affect Schedule (PANAS; Watson et al., 1988)	Self-administered
Engagement	Utrecht Work Engagement Scale–Student Version (UWES-S; Schaufeli & Bakker, 2003)	Self-administered
Relationships	Social Connectedness Scale (SCS; Lee & Robbins, 1995)	Self-administered

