##### Moderation and mediation analyses

2.2.9.2

Moderation and mediation analyses will be conducted as exploratory and hypothesis-generating analyses for the PPIA, PPIA+M, and WLCG groups. These analyses are not part of the primary confirmatory testing framework and will not be interpreted as demonstrating causal mechanisms.

Moderation analyses will be conducted using regression models including treatment condition, the candidate moderator, and the treatment-by-moderator interaction term. Continuous variables will be mean-centered to improve interpretation, following the recommendations of Kraemer and Blasey (65). Potential moderators will include baseline sociodemographic, academic, and clinical variables, adherence, and satisfaction with the intervention. Evidence of moderation will be considered present when the treatment-by-moderator interaction term is statistically significant, indicating that the effect of the intervention on well-being outcomes varies according to the level of the moderator.

Mediation analyses will examine whether changes in PERMA dimensions —positive emotion, engagement, relationships, meaning, and accomplishment— are associated with changes in emotional well-being and psychological, emotional, and social well-being. Changes in WEMWBS and MHC-SF scores between baseline and post-intervention will be used as dependent variables, treatment condition as the independent variable, and changes in PERMA dimensions between baseline and post-intervention as potential mediators. Indirect effects will be estimated using bias-corrected bootstrap confidence intervals with 5,000 resamples. Because mediator and outcome changes are assessed over overlapping time intervals, these analyses will be considered exploratory and will not be interpreted as demonstrating causal mechanisms.

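### The exploratory mediation and moderation models name no baseline score, which costs power on the randomised treatment-to-mediator path and in the moderation tests, and leaves the mediator-outcome slope dependent on an untested data model

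*Protocol article*

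**What the plan says.** Section 2.2.9.2 of the protocol article defines the mediation model in some detail. The outcome and predictor are given as: "Changes in WEMWBS and MHC-SF scores between baseline and post-intervention will be used as dependent variables, treatment condition as the independent variable". The mediators are "changes in PERMA dimensions between baseline and post-intervention as potential mediators". On inference it says: "Indirect effects will be estimated using bias-corrected bootstrap confidence intervals with 5,000 resamples". For moderation it says: "Moderation analyses will be conducted using regression models including treatment condition, the candidate moderator, and the treatment-by-moderator interaction term". No T1 score is named as a covariate in either model, and the moderation paragraph does not say whether the outcome is the T2 score or the change.

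Section 2.2.7 and Table 2 have the PERMA and well-being scales administered at T1, T2 and T3, so the baseline scores will be available. Section 2.2.4 assumes "correlation among repeated measures = .50". Section 2.2.9.2 also limits the use of the mediation results: because the intervals for mediator and outcome overlap, "these analyses will be considered exploratory and will not be interpreted as demonstrating causal mechanisms". The Introduction places mediators and moderators among the primary objectives, labels their analysis exploratory, and intends the results to guide later refinement of the intervention.

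**The concern.** Two separate issues follow from leaving the T1 scores out.

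The first is precision. Unless the T1–T2 correlation is very high, a raw change score is noisier than a T2 score adjusted for its own baseline. Arm is randomised, so the adjustment does not bias the treatment-to-mediator path or the treatment-by-moderator interaction. The lost power buys nothing.

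The second is the mediator-outcome slope, which is not randomised. If students who start low on a PERMA scale also start low on well-being, and low scorers drift upwards on both, the two changes are correlated even when the mediator does nothing. A PERMA dimension that treatment moves could then look like a mediator. The caveat in Section 2.2.9.2 gives overlapping intervals as its reason, which is a different problem.

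At stake is which PERMA dimensions and which subgroups are carried forward when the intervention is revised.

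**Working it through.** **Inputs.** From Section 2.2.4: correlation rho = .50, f = 0.16 (about d = 0.32), alpha .025, 47 per arm analysed and 59 recruited. Assumed, because the article does not give them: the baseline mediator-outcome correlation r (.3 to .7), a two-sided .05 level for these analyses, and d up to .50. Effects are in SDs of a single-occasion score, and the contrast is one active arm against the waiting list.

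**The plan's own figure.** For the group-by-time test, lambda = f² × N × m/(1 − rho) = 0.0256 × 141 × 3/0.5 = 21.66 on 4 and 276 df. Power is .951, as stated. Then 141/0.8 = 176.25, which rounds up to 177. The figures reproduce, so rho = .50 is used below. No power is stated for mediation or moderation.

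**Treatment-to-mediator path.** Residual variance in units of sigma²:
- change score: 2(1 − rho) = 1.00
- adjusted for T1: 1 − rho² = 0.75

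The ratio is (1 + rho)/2 = 0.75. Adjustment at 47 per arm is therefore worth about 47/0.75 = 63 per arm without it. Noncentrality is d/(SD × √(2/n)), with √(2/47) = 0.206.

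| n per arm | d | change score | adjusted |
|---|---|---|---|
| 47 | .32 | 34% | 43% |
| 47 | .50 | 67% | 79% |
| 59 | .32 | 41% | 51% |
| 59 | .50 | 77% | 87% |

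The gain is about 9 to 12 points. At d = .32 it falls to about 7 points if rho = .7 (ratio .85) and to about 4 if rho = .8 (ratio .90). At d = .20 and rho = .50 it is 4 to 5 points.

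**Moderation.** At rho = .50 the T2 score has variance 1.00 and the change score has 2(1 − .50) = 1.00, so the unstated choice of outcome does not matter here. For a moderator scaled to SD 1 and roughly unrelated to the T1 outcome score, the slope difference between two arms has the same standard error as the mean difference above. A slope difference of .32 to .50 SD per SD of moderator therefore gains about the same 9 to 12 points.

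**Indirect effect.** Simulated at rho = .50, with T2 depending on T1:
- Slope b = .5, 47 per arm: about 33% against 42% (d = .32), and 67–69% against 78–81% (d = .50).
- Slope b = .3: the gain from adjustment ranges from about −3 to +10 points.
- Slope b = .2: the change-score model usually rejects more often, by up to 27 points, because its slope is biased upwards.

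**Mediator-outcome slope with no true link.**

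*T2 depends on T1 (autoregressive).* Each change contains −(1 − rho) times its baseline, so the covariance of the changes is (1 − rho)²r and the slope is (1 − rho)²r/[2(1 − rho)] = (1 − rho)r/2. For r = .3, .5 and .7 this is .075, .125 and .175. The adjusted slope is 0.

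*Stable trait plus independent state noise.* All mediator-outcome covariances equal r, so the covariance of the changes is r − r − r + r = 0 and the change-score slope is 0. In the adjusted model the T1 and T2 mediator scores share a coefficient b, and T1 well-being has coefficient c. The normal equations are b(1 + rho) + rc = r and 2rb + c = rho, which give b = r(1 − rho)/(1 + rho − 2r²). At r = .4 this is .20/1.18 = .17.

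Simulated false mediation at 47 per arm and d = .50, requiring both paths to be significant at .05 (in place of the bootstrap):

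| data model | change scores | baseline-adjusted |
|---|---|---|
| autoregressive, r = .5 | 14.6% | 4.2% |
| stable trait, r = .4 | 3.3% | 28.8% |

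If treatment does not move the mediator, change scores flag at most 2.3% of trials under the autoregressive model.

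**The case against.** The strongest reply is that change score against baseline adjustment is an old and legitimate choice for a non-randomised path, and that nothing in the article favours the autoregressive model. Well-being and PERMA scales plausibly share a stable component, and in that case the change score is the safer estimator. This stands. A reader might infer that the plan creates false mediation and that adjusting for T1 removes it. The documents do not support that: rho = .50 fits both models, and under one of them replacing the change scores would introduce the error.

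The reply also notes that the large false-mediation rates need d near .50 and a sizeable r, whereas the article anticipates about .32 and gives no r. That stands too. A reader might further take the 9 to 12 points as a loss for the indirect effect in general. They are not, as the results for b = .2 and .3 show.

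Next, these analyses are exploratory, causal readings are barred, and a fuller plan might add covariates. The label limits what may be claimed, but it is no reason to give up precision that is free. The article does more than stay silent on mediation, since it fixes outcome, predictor, mediators and interval method. The moderation limb is weaker, because the stated terms need not be the only ones. There the request is simply to name the T1 outcome.

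**Conclusion.** The point holds in a limited form. Without T1 scores, the randomised treatment-to-mediator path loses about 9 to 12 points of power at rho = .50 and d between .32 and .50, and the moderation tests lose a similar amount. This rests on the plan's own rho and sample size and on an assumed .05 level. It does not depend on how mediator and outcome are related. The loss is smaller if rho is higher or the effect is smaller.

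For the mediator-outcome slope the finding is model dependence, not a demonstrated error. Change scores mislead if T2 depends on T1 and treatment moves the mediator. Adjusted scores mislead under a stable trait. The plan commits to one estimator without a reason and has the data to show both. The primary mixed models and their conclusions are untouched.

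**What to change.** In Section 2.2.9.2:

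1. Estimate the treatment-to-mediator path as the T2 PERMA score on arm, adjusted for the T1 PERMA score and T1 WEMWBS or MHC-SF.
2. Add the T1 score of the outcome to every moderation model, and state whether the outcome is the T2 score or the change.
3. Estimate each indirect effect twice: from T2 models adjusted for both T1 scores, and from change scores as now planned. Report both, and treat a PERMA dimension as a candidate mediator only when they agree.
4. Add to the existing caveat that the mediator-outcome slope depends on how T2 scores relate to T1 scores.

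The cost is wording, one or two degrees of freedom per model and one extra set of exploratory results. No new data are needed. Requiring agreement is stricter than either analysis alone, so some true mediators will be left undecided.

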#### Exit strategy

2.2.10

An exit strategy will be implemented in two key scenarios: (1) when a participant decides to withdraw from the study prematurely, and (2) at the official conclusion of the trial. In cases of premature withdrawal, a voluntary exit phone call will be conducted to document the reasons for leaving through a structured questionnaire. At the end of the study period, which includes a five-week intervention period followed by a six-month follow-up, participants will be informed about the transition and closure of the research.

## Discussion

3

This study will evaluate the efficacy of a brief positive psychology–based psychological intervention grounded in the PERMA model, delivered via a mobile application (PPIA) and through a blended format incorporating weekly multiconference telephone sessions (PPIA+M). The target population consists of university students, who face unique developmental, academic, and social stressors that increase their vulnerability to distress. Grounded in previous research on positive psychology and digital interventions (20, 24, 26, 28), the intervention systematically incorporates the five PERMA domains—Positive Emotion, Engagement, Relationships, Meaning, and Accomplishment—into a structured digital program. In line with evidence on telephone-based psychosocial support (30, 32–34), we hypothesize that both active intervention groups will outperform the waitlist control, with PPIA+M yielding higher adherence and impact due to added human contact.

The design of this intervention aligns with established best practices in prevention and mental health promotion among students, incorporating evidence-based elements positive psychology and cognitive-behavioral interventions while addressing the known barriers to access and engagement (25, 27). The PERMA framework (20) provides theoretical consistency and breadth, as it addresses psychological functioning beyond symptom reduction. This multidimensional focus makes it particularly suitable for prevention in nonclinical populations such as university students.

This study also proposes the use of ICTs to enhance accessibility and engagement. The mobile app enables flexible, autonomous completion of psychoeducational and experiential tasks, offering accessibility, scalability, and cost-efficiency. The PPIA+M condition introduces synchronous group contact via weekly multiconference calls. This blended approach is expected to maximize engagement, adherence, and therapeutic outcomes (30, 35) by enhancing motivation, strengthening therapeutic alliance, and fostering community (33).

The methodological rigor of this study is reinforced by adherence to updated SPIRIT 2025 (37) recommendations for clinical trial protocols and was informed by CONSORT 2025 (36) guidelines where applicable. Specifically, the protocol complies with SPIRIT recommendations regarding trial registration, specification of eligibility criteria, detailed description of interventions, outcome specification with validated instruments, sample size determination, randomization procedures, blinding of outcome assessment, and statistical analysis methods. In line with CONSORT, the study ensures a comprehensive description and manualization of interventions, training and supervision of facilitators, monitoring of fidelity, specification of comparator groups, use of psychometrically robust outcome measures, reporting of adherence and attrition, and inclusion of mediation and moderation analyses to clarify mechanisms of change. The intervention is fully manualized, facilitators receive training with fidelity checks, and blinded evaluators will use validated instruments. The primary outcomes—emotional well-being and psychological, emotional, and social well-being—will be assessed using the Warwick–Edinburgh Mental Well-Being Scale (WEMWBS) and the Mental Health Continuum–Short Form (MHC-SF).

However, some limitations should be acknowledged. First, the sample will be drawn from a single university, which may limit the generalizability of the findings to other academic or cultural contexts, and participation will be voluntary, raising the possibility of self-selection bias. Voluntary enrollment may attract students with higher baseline motivation, greater interest in psychological well-being, or greater readiness to engage in self-guided activities. Second, outcomes will rely primarily on self-report measures, which may be subject to social desirability bias, reporting biases, and measurement fatigue across repeated assessments. Third, the use of a waiting list control group, while ethically and practically justified, may lead to an overestimation of intervention effects compared with active control conditions. Moreover, this passive comparator does not allow the specific active ingredients of the PERMA model to be isolated from non-specific factors such as digital novelty, participant expectancy, structured self-monitoring, or human support. Therefore, any efficacy findings should be interpreted as supporting the effectiveness of the intervention package relative to no immediate intervention, rather than demonstrating the specific incremental value of the PERMA components alone. Fourth, adherence is expected to play a critical role in determining intervention effectiveness, particularly in self-guided digital formats. Because telephone multiconference support will be delivered in small groups and facilitated by trained psychologists, minor peer-group or facilitator effects cannot be completely ruled out. Although these effects are expected to be limited because the sessions are brief, manualized, and focused on adherence feedback rather than group psychotherapy, they should nevertheless be considered when interpreting differences between PPIA and PPIA+M. Future studies should replicate these findings using multisite samples, active comparators, and complementary assessment strategies.

In conclusion, this research is innovative in testing a brief, theoretically grounded PERMA-based intervention through digital and hybrid delivery. If efficacious, it could be adopted across academic contexts as a scalable, cost-effective, and engaging tool to promote student mental health. By addressing methodological gaps, integrating technology with human support, and focusing on resilience and academic functioning, this study could inform future interventions for young adults and generate impact across academic, clinical, and social domains.
